# IMNI PRECISION trial protocol: a phase II, open-label, non-inferior randomized controlled trial of tailoring omission of internal mammary node irradiation for early-stage breast cancer

**DOI:** 10.1186/s12885-022-10454-1

**Published:** 2022-12-27

**Keywords:** Clinical trial, Clinical-genomic model, Breast cancer, Precision radiotherapy, Internal Mammary Node Irradiation

## Abstract

**Background:**

Since the publication of MA-20 and EORTC-22922 trials, chest wall (CW)/ whole breast (WB) irradiation + comprehensive regional nodal irradiation (RNI) with internal mammary node irradiation (IMNI) has been the standard adjuvant treatment for early-stage breast cancer (BC). However, one size does not fit all BC, and the risk of recurrence significantly varies among this patient population. In addition, whether all BC patients presented with one to three positive lymph nodes (pN1) could benefit from IMNI remains controversial. Thus, the optimal adjuvant RNI volume for early-stage BC with T1-2N1 remains undetermined.

**Methods:**

The IMNI PRECISION trial is a single institute, open-labeled, non-inferior, randomized controlled trial. A total of 214 clinically “high risk” BC patients which is characterized as having at least two of the five clinically adverse factors (age ≤ 40, three positive LN, T2 stage, grade 3 and Ki-67 index ≥ 14%), but genomic score “low risk” (the genomic score ≤ 44) N1 breast cancers are randomly assigned to omitting IMNI group (experimental group) or with IMNI (control group) with a 1:1 ratio. The primary endpoint of this trial is event-free survival, and secondary endpoints include overall survival and locoregional recurrence-free survival.

**Discussion:**

The IMNI PRECISION design allows promising clinical-genomic model to stratify the individualized risk of developing recurrence and guides the optimal RNI treatment for early-stage (pT1-2N1) BC patients. We anticipate that our results would provide high-level evidence to tailor IMNI according to individualized recurrence risk of BC.

**Trial registration:**

ClinicalTrials.gov Identifier NCT04517266. Date of registration: August 18, 2020. Status: Recruiting.

**Supplementary Information:**

The online version contains supplementary material available at 10.1186/s12885-022-10454-1.

## Background

In 2020, female breast cancer (BC) has become the commonly diagnosed tumor and the fifth leading cause of cancer-related death worldwide, with 2.3 million new cases and 685,00 deaths each year [1]. Two largest individual meta-analyses performed by Early Breast Cancer Trialists' Collaborative Group (EBCTCG) have found that adjuvant radiotherapy (RT) could significantly decrease the risk of developing recurrence and improve long-term outcomes of early stage BC patients underwent breast-conserving surgery(BCS) [2] or mastectomy [3]. Therefore, adjuvant RT plays an important role in the multidisciplinary management of early-stage BC. However, the optimal regional nodal irradiation (RNI) volume for early-stage BC remains controversial. In two large phase III randomized controlled trials (MA-20 and EORCT-22922), chest wall (CW)/whole breast (WB) + comprehensive RNI with IMNI significantly decreases the disease-free survival (DFS) and BC mortality for high risk N0 and pN1 BC patients [4–6]. Based on these results, comprehensive RNI with IMNI for pN1 patients is strongly recommended by the National Comprehensive Cancer Network (NCCN) guideline. On the other hand, in a recent phase III trial performed by Suh C.O. et al., the authors find that comprehensive RNI including IMNI does not significantly improve the DFS among node-positive BC patients, while subgroup analysis indicates that patients with primary tumor located with medially or centrally could might benefit from additional IMNI [7]. As a result, one size does not fit for all early-stage BC as this patient population is a heterogenous disease. Until now, the optimal RNI volume for pN1 BC remains undetermined.

Since IMNI would inevitably increase the lung and heart radiation dose, which might be related with an increased risk of developing cardiac or pulmonary toxicities [8]. Thus, in clinical practice, histological classification of breast tumors has been instrumental in determining a more personalized approach for pN1 breast cancer. Indeed, multiply studies have been performed to stratify clinical “high risk” early-stage BC patients who might be obtained from adjuvant post-mastectomy radiotherapy (PMRT) [9–14]. In consistent with those previous reports, our institution establishes and validates a prognostic nomogram including five risk factors (age, number of positive LN, tumor size, grade and Ki-67) accurately predict 5-year BC specific survival after mastectomy without adjuvant radiotherapy, which provides a practical stratification system to identify “high-risk” BC patients who might be indicated for adjuvant RT [15]. Subsequently, we validate this risk stratification model to individualize the adjuvant RT strategy among pT1-2N1 BC treated with modern systemic therapy, our result indicates that PMRT is an independent prognostic factor for DFS (HR 0.50, *p* = 0.05) among the clinical “high-risk” patients. However, those clinical “high-risk” patients could not benefit from comprehensive RNI with IMNI compared to those without IMNI (*p* > 0.05) [16]. In comparison with clinical risk model based on histopathologic factors, multi-genomic expression would provide individualized prognostic information for BC patients. Currently, multi-genomic expression profiling, such as 21-gene recurrence score and PAM-50-based 46-gene assay, has been recommended by international guidelines to tailor systemic therapy for patients with early-stage BC, but the clinical implications of multi-genomic expression for guiding radiotherapy is less well established. In a secondary analysis of a prospective trial of NSABP (National Surgical Adjuvant Breast and Bowel Project) B-14 and B-20,the authors find that the 21-gene Recurrence Score is an independent risk factor for locoregional recurrence in the cohort of 895 hormonal receptor (HR) positive patients treated with tamoxifen (HR2.16, 95%CI: 1.26–3.68, *p* = 0.005) [17]. In another retrospective analysis based on the Austrian Breast and Colorectal Cancer Study Group (ABCSG) 8 trial, the authors demonstrate that PAM-50 could be used to identify high local recurrence risk among postmenopausal HR-positive BC received with hormonal therapy, but it is not a predictive factor for obtaining from adjuvant RT [18]. RecurIndex, combined with 18 cancer genes and 10 reference genes, is a multigene profiling assay based on Chinese 28 genes, which could be used to predict the risk of local recurrence and distant metastasis for BC patients [19–22]. Our research team have demonstrated that the 5-year local–regional recurrence (LRR) free survival rates are 95–100% for N0 and N1 mastectomy BC patients with the 18-gene scores of < 44, while the LRR-free survival rate decreases to only 27–51% among BC patients with the 18-gene scores of more than 44 [23]. Thus, the 18-gene recurrence score might be used to identify biologically “high risk” breast cancer patients who would benefit from IMNI. Currently, to our best knowledge, there is no prospective studies to specifically investigate the role of IMNI in pN1 BC according to clinical-genomic model. As a result, we design this prospective trial by using an established clinical risk model combined with 28-gene score (RecurIndex) to individually stratify the risk of pN1 BC, and then to investigate whether those clinical “high-risk”, but genomic “low risk” pN1 BC patients would be safely omitting IMNI. Based on the Standard Protocol Items: Recommendations for Interventional Trials (SPIRIT) guidelines, our research team write the prospective trial protocol.

## Materials/design

### Hypothesis

We hypothesize that clinical risk model combined genomic model could individually define the risk of developing recurrence among early-stage BC patients, and those clinically high risk but genomic score “low risk” BC patients would be safely omitted from IMNI.

### Objectives

The primary objective of this prospective non-inferior, RCT aims to investigate whether clinically “high risk”, but genomic score “low risk” early-stage BC would be safely omitted from IMNI.

## Methods

### Trial design

This is a prospective, non-inferiority, open-labeled, randomized controlled trial. We recruit histo-pathologically confirmed invasive breast cancer patient with pT1-2N1 after curative surgery from Ruijin Hospital, Shanghai Jiaotong university school of medicine. We initially use the clinical model to identify the clinically “high risk” of developing recurrence BC patients, defining as having at least two of the five clinical risk factors (age ≤ 40, three positive LN, T2 stage, grade 3 and Ki-67 index ≥ 14%). The formalin-fixed and paraffin-embedded (FFPE) tumor samples of those clinically “high-risk” BC would be detected using RecurIndex test, which is a multi-genomic test established according to Chinese 28 genes [19, 20]. Based on previous research, the accuracy of RecurIndex for predicting local–regional recurrence (LRR) in BC patients could be up to 93% by using 44 score as the threshold value for high or low risk. Therefore, patients with score ≤ 44 are classified as genomic low risk, > 44 are regarded as genomic high risk [23]. For early-stage BC patients with clinically “high risk” and genomic high risk, CW/WB + comprehensive RNI with IMNI would be recommended. For early-stage BC patients with clinically “high risk” but genomic low risk, these patients will be randomly assigned to RNI omitting IMNI (experimental group) or RNI with IMNI group (controlled group) with a 1:1 allocation ratio. Randomization was conducted with computer-generated random number by using SPSS software version 21.0 (IBM Corporation, Armonk, NY, USA). Participants will be followed until death or drop out of the study. Figure 1 shows the design of the IMNI PRECISION trial.

**Fig. 1 Fig1:**
[figure not shown]
the design of the IMNI PRECISION trial

### Participants

To compared the non-inferior difference of 5-year event-free survival for RNI omitting IMNI vs. RNI with IMNI group among early-stage BC with early-stage BC patients with clinically “high risk” but genomic low risk, a total of 214 patients will be recruited.

The detailed instruction of present study would be offered to every potential participant before enrollment, and each enrolled patients should sign the informed consent.

### Inclusion criteria

(1) histologically diagnosed invasive carcinoma of the breast; (2) treated with radical surgery either mastectomy or BCS combined with axillary lymph node dissection or sentinel lymph node biopsy; (3) patients had 1–3 positive lymph node (pN1); (4) presented with at least 2 clinical risk factors; (5) female patients aged between 18 and 80 years old; (6) ECOG performance status ≤ 2 or Karnofsky ≥ 70%; (7) anticipated OS > 5 years; (8) Pathologically surgical margin is negative; (9)hormonal receptor, HER2 (human epidermal growth factor receptor 2) and Ki67 index can be tested for the primary breast tumor; (10) women of child-bearing potential should use adequate contraception for up to 1 month before enrolling the trial; (11) patients are able to understand and willing to participate the trial and signed consent form could be obtained.

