### Exclusion criteria

(1) metastatic ipsilateral supraclavicular lymph node; (2) involvement of ipsilateral internal mammary lymph nodes; (3) Pregnant or lactating women; (4) patients received with breast reconstruction surgery; (5) Severe non-neoplastic medical comorbidities; (6) History of non-breast malignancy within 5 years with the exception of lobular carcinoma in situ, basal cell carcinoma of the skin, carcinoma in situ of skin and carcinoma in situ of the cervix; (7) simultaneous bilateral breast cancer; (8) had a history of radiotherapy to the neck, chest and/or ipsilateral axillary region; (9) presented with active collagen vascular disease; (10) presented with distant metastatic disease; (11) the primary breast tumor is unresectable; (12) Interval between radical surgery and radiotherapy was longer than 3 months or interval between last dose of adjuvant chemotherapy and radiotherapy was more than 8 weeks.

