### Interventions

#### Omitting IMNI group (experimental group)

Irradiation would be delivered to chest wall or whole breast combined with supra/infraclavicular nodes, and IMNI is omitting. Both hypofractionated or conventional intensity-modulated radiation therapy for BC are allowed. The hypofractionated prescribed dose is 40.05 Gy/15 Fx, with a tumor bed boost for breast conserving surgery (BCS) patients at a total dose of 10.68 Gy/4 fractions. And the conventional prescribed dose is 50 Gy/25Fx for CW/WB followed by a tumor-bed boost with 10 Gy/5Fx. It is recommended that 95% of the PTV covers 100% of the prescribed dose and the acceptable variation is that 90% of the PTV covers 100% of the prescribe dose, the maximum dose of the PTV should be less than 120% of the prescribed dose.

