#### IMNI group (controlled group)

Irradiation would be delivered to chest wall or whole breast combined with comprehensive regional nodal areas including internal mammary node. The prescribed dose is the same as the omitting IMNI group, both hypofractionated or conventional intensity-modulated radiation therapy for BC are allowed. It is recommended that 95% of the PTV covers 100% of the prescribed dose and the acceptable variation is that 90% of the PTV covers 100% of the prescribe dose, the maximum dose of the PTV should be less than 120% of the prescribed dose.

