#### Allocation

Once obtaining a signed informed consent, each eligible participant would be randomized to omitting IMNI group or IMNI group (1:1) based on a computer-generated random number.

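### As published, inclusion criterion 10 sets a maximum of one month of contraception and ends it at enrolment, before radiotherapy begins: a minor patient-safety wording error

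*Protocol article*

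**What the plan says.** The protocol article, Inclusion criteria, item 10, states: "women of child-bearing potential should use adequate contraception for up to 1 month before enrolling the trial". Women who may become pregnant are eligible, since item 5 of the same list admits "female patients aged between 18 and 80 years old".

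The only other provision on pregnancy is item 3 of the Exclusion criteria, "Pregnant or lactating women". The article does not mention contraception again.

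On the order of events, the Allocation section says: "Once obtaining a signed informed consent, each eligible participant would be randomized to omitting IMNI group or IMNI group". Table 1 (follow-up schedule) puts eligibility screening, informed consent and randomisation in the pre-radiotherapy column, and both interventions in the column for the radiotherapy period.

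On the exposure, the section on the experimental group says: "Both hypofractionated or conventional intensity-modulated radiation therapy for BC are allowed". The section on the control group says: "The prescribed dose is the same as the omitting IMNI group".

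**The concern.** A contraception rule in a radiotherapy trial is there to prevent a pregnancy from being present at the start of irradiation or beginning during it. To do that, it needs a minimum duration before entry and a period that reaches to the end of treatment. Criterion 10 states a period and gets both ends wrong: the duration is capped instead of having a floor, and the period stops at enrolment.

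What is at stake is the clarity of a safety-related eligibility line. Staff who check eligibility cannot use it as a test, because no duration is too short to pass. A woman who meets it as written is not asked by it to use contraception while she is being irradiated.

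**Working it through.** The article gives no figure to reproduce on this point. The check is a reading of the sections against one another, plus a sum of the fractions.

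**Step 1: duration.** The criterion allows a period of *up to* 1 month. If d is the time on contraception before enrolment, the literal condition is 0 ≤ d ≤ 1 month. A usable criterion would be d ≥ 1 month. The two agree only at exactly 1 month. Read literally, d = 0 passes and a woman with long-standing contraception exceeds the stated maximum, which cannot be what was meant.

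**Step 2: anchor.** Set in order, the events are:

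| Event | Source | Inside the stated contraception period? |
|---|---|---|
| Up to 1 month before enrolment | Inclusion criteria, item 10 | Yes |
| Screening, consent, randomisation | Allocation; Table 1, pre-radiotherapy column | The period ends here |
| Radiotherapy, either arm | Interventions; Table 1, radiotherapy column | No |

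**Step 3: what the stated period leaves out.** The fractions come from the section on the experimental group, and the control group has the same prescription:

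- Hypofractionated, no boost: 15
- Hypofractionated with tumour-bed boost: 15 + 4 = 19
- Conventional, no boost: 25
- Conventional with tumour-bed boost: 25 + 5 = 30

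The whole course, 15 to 30 fractions, lies after the stated period. These counts describe the treatment that the wording does not reach. They do not measure harm.

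**Step 4: does anything else shown repair it?** Exclusion criterion 3 bars a woman who is pregnant or lactating at entry. It says nothing about conception during treatment. The Pre-treatment evaluation section and Table 1 contain no item that extends criterion 10 past enrolment. They are cited only to show that no other section corrects the line, not as further findings.

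**The case against.** The strongest reply is that this is a language slip combined with a silence that an article may keep. An inclusion criterion describes a patient at entry, and duties during treatment usually sit in the full protocol and the consent form. Neither is shown, although the Current trial status section refers to protocol Version 2.0. The article has other slips of English, and no investigator is likely to apply a contraception rule in a way that lets zero days pass.

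Much of this stands. The phrase is probably a slip, and the unseen documents may well cover the treatment period. It does not dispose of the point, because the article is not simply silent. It states a rule with a duration and an end point, and both are wrong for the rule's purpose. If the full protocol says something better, the published line still needs correcting.

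Three stronger readings are tempting, and the documents do not support them:

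- **The trial has no contraception requirement during radiotherapy.** This cannot be concluded from the article alone, for the reason just given. Nothing in criterion 10 tells a woman to stop contraception at enrolment.
- **Taking part adds fetal risk.** Both arms receive radiotherapy, and the Abstract describes regional nodal irradiation including the internal mammary nodes as standard adjuvant treatment. Randomisation does not create the exposure.
- **The design concentrates the problem in younger women**, because age 40 or younger is one of the five factors in the entry rule ("defining as having at least two of the five clinical risk factors"). The article gives no age distribution or factor prevalences, and the genomic score selects further before randomisation. The number of women affected cannot be inferred.

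**Conclusion.** The point holds as a minor wording correction. Read literally, criterion 10 sets a ceiling of 1 month where a floor is needed, and its period closes before the 15 to 30 fractions given in either arm. No other section of the article corrects it.

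Its consequence is limited to patient-safety wording. The line is the same in both arms, so bias, power, sample size and analysis are untouched. The documents do not give the number of women of child-bearing potential, so no pregnancy risk is estimated. The conclusion assumes only that the published sentence matches the criterion in use. If the full protocol or consent form already has the right period, the error is confined to the article.

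**What to change.** Reword criterion 10 so that any woman who could become pregnant must use adequate contraception from at least 1 month before enrolment through the end of radiotherapy. This replaces the ceiling with a minimum and carries the period across treatment. Then check that the full protocol and the consent text say the same.

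The cost is one amended eligibility line, reviewed by the hospital's ethics committee under the route given in Data collection and management. No procedure is added. At the last status given, 75 of the planned 214 patients had been enrolled by 30 July 2022 and recruitment was open, so a correction at that stage could reach up to 214 − 75 = 139 later participants. If the full protocol is already right, only the published wording needs correcting.

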### Exclusion criteria

(1) metastatic ipsilateral supraclavicular lymph node; (2) involvement of ipsilateral internal mammary lymph nodes; (3) Pregnant or lactating women; (4) patients received with breast reconstruction surgery; (5) Severe non-neoplastic medical comorbidities; (6) History of non-breast malignancy within 5 years with the exception of lobular carcinoma in situ, basal cell carcinoma of the skin, carcinoma in situ of skin and carcinoma in situ of the cervix; (7) simultaneous bilateral breast cancer; (8) had a history of radiotherapy to the neck, chest and/or ipsilateral axillary region; (9) presented with active collagen vascular disease; (10) presented with distant metastatic disease; (11) the primary breast tumor is unresectable; (12) Interval between radical surgery and radiotherapy was longer than 3 months or interval between last dose of adjuvant chemotherapy and radiotherapy was more than 8 weeks.

### Pre-treatment evaluation

History and physical examination: assessment of ECOG status, histology of cardiovascular disease, height, weight; comorbidities;Blood test: blood cell count; liver and renal function; myocardial enzymes; thyroid function test;Image examinations: breast ultrasonography or breast magnetic resonance imaging (MRI); chest CT, regional nodal ultrasonography; ultrasonography of liver;Cardiac examination: Twelve-lead electrocardiogram; echocardiography;

### Radiotherapy

We contour the clinical target volume (CTV) on all CT slices if these structures are visible based on RUIJIN guideline [24], and contour the organs at risk (OAR) based on Radiation Therapy Oncology Group (RTOG) contouring guideline [25]. The recommended dose constraints for OARs and required dose coverage of plan treatment volume (PTV) are summarized in supplemental Tables 1 and 2.

### Interventions

#### Omitting IMNI group (experimental group)

Irradiation would be delivered to chest wall or whole breast combined with supra/infraclavicular nodes, and IMNI is omitting. Both hypofractionated or conventional intensity-modulated radiation therapy for BC are allowed. The hypofractionated prescribed dose is 40.05 Gy/15 Fx, with a tumor bed boost for breast conserving surgery (BCS) patients at a total dose of 10.68 Gy/4 fractions. And the conventional prescribed dose is 50 Gy/25Fx for CW/WB followed by a tumor-bed boost with 10 Gy/5Fx. It is recommended that 95% of the PTV covers 100% of the prescribed dose and the acceptable variation is that 90% of the PTV covers 100% of the prescribe dose, the maximum dose of the PTV should be less than 120% of the prescribed dose.

#### IMNI group (controlled group)

Irradiation would be delivered to chest wall or whole breast combined with comprehensive regional nodal areas including internal mammary node. The prescribed dose is the same as the omitting IMNI group, both hypofractionated or conventional intensity-modulated radiation therapy for BC are allowed. It is recommended that 95% of the PTV covers 100% of the prescribed dose and the acceptable variation is that 90% of the PTV covers 100% of the prescribe dose, the maximum dose of the PTV should be less than 120% of the prescribed dose.

